## Abstract

**Background:**

Hypoglycaemia, especially nocturnal, remains the main limiting factor of achieving good glycaemic control in type 1 diabetes.

The effect of first generation long-acting insulin analogues in reducing nocturnal hypoglycaemia is well documented in patient with type 1 diabetes. The effect of the newer long-acting insulin degludec on risk of nocturnal hypoglycaemia remains undocumented in patients with type 1 diabetes and recurrent severe nocturnal hypoglycaemia.

The HypoDeg trial is designed to investigate whether insulin degludec in comparison with insulin glargine U100 is superior in limiting the occurrence of nocturnal hypoglycaemia in patients with recurrent nocturnal severe hypoglycaemia. This paper reports the study design of the HypoDeg trial.

**Methods/design:**

A Danish investigator-initiated, prospective, randomised, open, blinded endpoint (PROBE), multicentre, two-year cross-over study investigating the effect of insulin degludec versus insulin glargine U100 on frequency of nocturnal hypoglycaemia in patients with type 1 diabetes and one or more episodes of nocturnal severe hypoglycaemia during the preceding two years as the major inclusion criteria. Patients are randomised (1:1) to basal therapy with insulin degludec or insulin glargine. Insulin aspart is used as bolus therapy in both treatment arms.

**Discussion:**

In contrast to most other insulin studies the HypoDeg trial includes only patients at high risk of hypoglycaemia. The HypoDeg trial will compare treatment with insulin degludec to insulin glargine U100 in terms of risk of nocturnal hypoglycaemic episodes in patients with type 1 diabetes with the greatest potential to benefit from near-physiological insulin replacement therapy. www.clinicaltrials.gov: NCT02192450.

## Background

Hypoglycaemia is the main side-effect of insulin therapy in type 1 diabetes and remains a major source of daily concern for patients and their relatives. Nocturnal hypoglycaemia, in particular, is a barrier against achievement of good glycaemic control as the fear of these episodes may impose inappropriate avoidance behaviour resulting in overnight hyperglycaemia in many patients [1]. Reduction of nocturnal hypoglycaemia in type 1 diabetes is therefore important to improve overall glycaemic control.

Improved basal insulin therapy has consistently resulted in reduced risk of nocturnal hypoglycaemia. Thus, the first-generation insulin analogues insulin glargine U100 and insulin detemir both reduce nocturnal hypoglycaemia by 26–53% compared to NPH insulin [2–4]. Insulin detemir reduces the risk of nocturnal (severe and non-severe) hypoglycaemia even in patients with type 1 diabetes and recurrent severe hypoglycaemia [5–8]. However, nocturnal hypoglycaemia remains a clinical challenge even with the use of these insulin analogues.

Insulin degludec is a newer long-acting basal insulin with a half-life of more than 24 h [9]. A recent study has demonstrated a significantly lower day-to-day variability than insulin glargine U100 – a coefficient of variation (CV) of 21% versus 83%, respectively [10]. Two phase 3 trials and a meta-analysis involving patients with type 1 diabetes have demonstrated lower rates of nocturnal hypoglycaemia with insulin degludec compared to insulin glargine U100 [11–13]. Like most other insulin trials, however, these trials only included participants at low risk of hypoglycaemia and accordingly the absolute risk reduction of nocturnal hypoglycaemia with insulin degludec is small. The results from the phase 3 programme have been confirmed in the SWITCH1 trial, which included patients with type 1 diabetes and increased risk of hypoglycaemia (e.g. people with impaired hypoglycaemia awareness, previous severe hypoglycaemia, or impaired renal function) [14]. The SWITCH1 trial did not specifically study people at particular risk of severe nocturnal hypoglycaemia, which may be those with the greatest potential to benefit from insulin degludec. The effect of insulin degludec in limiting nocturnal hypoglycaemia remains undocumented in this high-risk type 1 diabetes population.

The aim of this study is to compare the effect of insulin degludec with insulin glargine U100 on risk of nocturnal hypoglycaemia in patients with previous severe nocturnal hypoglycaemia.

## Aims

The *primary aim* is to test the hypothesis that treatment with insulin degludec as compared to insulin glargine U100 results in lower risk of symptomatic nocturnal hypoglycaemia in patients with type 1 diabetes and high risk of severe nocturnal hypoglycaemia.

The *secondary aims* are – with reference to the American Diabetes Association (ADA) criteria for classification of hypoglycaemia [15] – to investigate the effect of insulin degludec compared to insulin glargine U100 on:Any hypoglycaemic episode (symptomatic, asymptomatic/silent, severe) analysed according to severity and/or time of dayMaintenance of baseline glycaemic control (HbA1c)Quality of life and depression/anxiety

## Methods/design

### Design, comparative treatment regimens and study duration

A Danish investigator-initiated, cross-over, multi-centre study conducted in a prospective, randomised, open, blinded endpoint (PROBE) design (Fig. 1). Patients are randomised to treatment with basal-bolus therapy with insulin degludec and insulin aspart (Tresiba®/NovoRapid®) or insulin glargine U100 and insulin aspart (Lantus®/NovoRapid®) in random order. Each treatment period lasts for 12 months. The first three months of each treatment period is a run-in or cross-over phase to be used for insulin dose adjustment and stabilisation of treatment regimens. Endpoints are assessed during the last nine months of each treatment arm (Fig. 1). Optional admissions for overnight plasma glucose measurements and six days of ambulatory blinded continuous glucose monitoring will be performed after 6 and 12 months in each treatment arm (Fig. 1).

**Fig. 1 Fig1:**
[figure not shown]
Study design.  Endpoint assessment periods.  Admission for overnight plasma glucose monitoring and/or 6 days of ambulatory 24 h continuous glucose monitoring

Insulin doses will be adjusted according to the individual patient’s need at the discretion of the individual physician. Patients are instructed to perform and record 4-point self-monitored blood glucose (SMBG) profiles twice per week (before breakfast, before lunch, before dinner and at bedtime). A treat-to-target design is deliberately not used in order not to intervene with present glycaemic control and everyday clinical practice, which in itself may interfere with the risk of hypoglycaemia. We expect the individual patient to present the best obtainable glycaemic control with respect to risk of hypoglycaemia at inclusion, and we therefore strive for maintenance of baseline glycaemic control in both treatment periods. If, however, the glycaemic control is not acceptable we will strive for the best obtainable glycaemic control in both treatment periods, taking the risk of hypoglycaemia into account.

The HypoAna trial [5] showed significantly increased rates of severe hypoglycaemia during run-in and cross-over periods. Therefore, insulin doses are reduced at entrance into both treatment arms. A 20% reduction in both basal and bolus insulin dose is recommended when the patient changes from one insulin regimen to another, irrespective of the product. Rapid up titration by mandatory phone consultations weekly at week 1, 2 and 4 is followed by ad hoc titration at the investigators’ discretion.

The study is a once daily (QD) comparison between the insulins with long duration of action, i.e. degludec and glargine. Insulin degludec and insulin glargine U100 are administered subcutaneously in the thigh or in the abdominal wall with the evening meal. Correct injection technique is assured by a diabetes specialist nurse. The site of injection should be changed within the same anatomical region to avoid lipohypertrophy making insulin absorption more unpredictable.

The study was approved by The Regional Committee on Biomedical Research Ethics.

(#H-3-2014-101), the Danish Medicines Agency (#2014071615) and the Danish Data Protection Agency (I-suite no: 02945; #NOH-2014-018). The study is registered at www.eudract.ema.europe.eu (#2014–001942-24) and at www.clinicaltrials.gov (# NCT02192450). The Study is conducted in accordance with the Helsinki Declaration.

### Participants

#### Pre-screening/pre-selection

Pre-screening/pre-selection approaches are used at the participating outpatient clinics.

The primary approach is a questionnaire, which is mailed to the patients or completed by the patients in the clinic. Patients with one or more episodes of nocturnal severe hypoglycaemia in the preceeding two years are interviewed by telephone to validate severity (need for assistance from others) and causality of the events.

#### Screening, in- and exclusion criteria

Patients with one or more episodes of nocturnal severe hypoglycaemia during the last two years are screened (*n* = 154) according to in- and exclusion criteria.

The inclusion criteria are type 1 diabetes for more than five years, one or more episodes of nocturnal severe hypoglycaemia in the previous two years (defined as need for third party assistance to restore blood glucose level), age > 18 years, treatment with multiple dose insulin injection (more than 2) or insulin pump allowing for both human insulin and insulin analogues, a negative pregnancy test, willingness to a once-daily (QD) regimen concerning basal insulin, willingness to do SMBG and keep a diary.

Exclusion criteria are history of primary or secondary adrenal or growth hormone insufficiency, untreated hypothyroidism, history of unstable angina or major cardiovascular events, heart failure (New York Hart Association (NYHA) class IV), history of malignancy unless a disease-free period exceeding five years, history of alcohol or drug abuse, pregnancy or lactation, and women of childbearing potential who are not using chemical or mechanical contraception, HbA1c > 86 mmol/mol (10%), and shifting working hours. Criteria for discontinuation are withdrawal of consent, pregnancy or non-compliance with the study protocol as judged by the investigator. Discontinuing patients are not substituted, but data on discontinuing patients are included in data analyses on an intention-to-treat basis.

Participants were included in the HypoDeg Trial from January 2015 to February 2017. Last patient, last visit expected in February 2019.

### Randomisation

Patients are randomised 1:1 to insulin degludec or insulin glargine. Treatment allocation will be obtained by a web-based electronic case report file (CRF). The randomisation will be in blocks of four on site. Treatment allocation will not be blinded to patients or study personnel caring for patients since insulin analogues differ in therir pharmacokinetic properties.

### Visit procedures

Patients are seen in the outpatient clinics at Nordsjællands Hospital, Steno Diabetes Center Copenhagen, Hvidovre University Hospital, Køge Hospital, Odense University Hospital, Copenhagen University Hospital (Rigshospitalet), Sydvestjysk Sygehus, Frederica Hospital, Aalborg Hospital and Aarhus University Hospital for 10 visits.

Prior to any protocol-related procedures written informed consent is obtained. At visit 0 (V0) patients are screened for in- and exclusion criteria and eligible patients are scheduled for enrolment in the treatment phase of the study. Information about demography, lifestyle and medical history including diabetes treatment history, diabetic complications and concomitant medication, is gathered at the screening visit. Frequencies of episodes of nocturnal symptomatic hypoglycaemia during the last month and severe hypoglycaemia within the previous two years (overall and nocturnal) are reported at V0 [16]. The patient’s insulin injection technique is tested and corrected, if needed, and patterns of insulin adjustment are clarified. A physical examination including vital signs and body measurements completes the screening visit.

At randomization (V1) the patients attend the clinic after an overnight fast to enable fasting blood samples (glucose and C-peptide). Urinary albumin excretion rate is estimated in one overnight urine sample, and a biobank of serum, plasma, DNA and urine samples are established and stored at − 80 °C to permit subsequent analyses of newly discovered relevant markers without further discomfort to the patient.

Autonomic dysfunction is evaluated by the Vagus^tm^ device (Medicus Engineering, Aarhus, Denmark), which provides data on active tests of autonomic dysfunction following guidelines and recommendations of ADA and the European Association for the Study of Diabetes (EASD) [17, 18]. A 12-lead electrocardiogram is recorded and visually assessed. State of hypoglycaemia awareness is classified by three validated methods. [16, 19–21]. Four questionnaires about quality of life are filled in: The EuroQol-5 dimension quality of life index (EQ-5D-3 L), the Insulin Treatment Satisfaction Questionnaire (ITSQ), the Hypoglycaemic Confidence Scale (HCS) and the Hypoglycemia Fear Survey (HFS).

Two questionnaires about depression and anxiety are used: The Symptom Checklist (SCL-92) and Major Depression Inventory (MDI) [22–24].

The procedures performed at the randomisation visit (V1), except randomisation, are repeated at cross-over (V5) and at the end of the study (V9). At every visit (V1-V9) vital signs (blood pressure and pulse) and body measurements (weight) are recorded and HbA1c is measured.

## Endpoint registration

### Hypoglycaemia assessment

Hypoglycaemic events will be recorded during each treatment period – during night-time and during daytime. Night-time is defined from four hours after evening bolus of short-acting insulin until time for actual morning bolus insulin administration. Night-time will also be analysed conventionally from 23:00 to 06:59 and from 00:00 to 05:59 (Fig. 2). Daytime is defined conventionally from 07:00 to 22:59 and from 06:00 to 23:59. Data from the last nine months of each treatment arm will be used for endpoint analyses.

**Fig. 2 Fig2:**
[figure not shown]
Definition of night. **a**: night is defined as time from 4 h after evening bolus of short acting insulin until time for actual morning bolus insulin administration. In the example shown the night is from 00:30 until 06:30, **b**: conventional definition of night from 23:00 to 06:59, **c**: conventional definition of night from 00:00 to 05:59

Hypoglycaemic endpoints are defined according to the latest ADA recommendations [15].

#### Documented mild symptomatic hypoglycaemia

Mild symptomatic hypoglycaemia is defined as an event during which typical symptoms of hypoglycaemia are accompanied by a measured plasma glucose concentration ≤ 3.9 mmol/l and treated without assistance from other persons. Patients are instructed and repeatedly encouraged to keep a diary on hypoglycaemia. Patients will report all events of symptomatic hypoglycaemia including date, time of episode, the accompanying measurement of plasma glucose, symptoms, awake or asleep, and time for last bolus insulin administration. In addition, all episodes occurring during night-time must be reported by telephone to a nurse within 24 h or first upcoming weekday after the event. All possible nocturnal symptomatic hypoglycaemic episodes will be adjudicated by an independent endpoint committee consisting of diabetes specialists blinded to the individual patient’s insulin regimen.

#### Asymptomatic hypoglycaemia

Asymptomatic hypoglycaemia is defined as an event not accompanied by typical symptoms of hypoglycaemia but with a measured plasma glucose concentration ≤ 3.9 mmol/l. Assessment of asymptomatic hypoglycaemia is accommodated in the 4-point SMBG profiles done twice a week and in the blinded CGM data obtained after 6 and 12 months in each treatment period.

Due to more recent hypoglycaemia guidelines [25] analyses of nocturnal symptomatic hypoglycaemia and any hypoglycaemic episode with a plasma glucose concentration ≤ 3.0 mmol/l are also planned.

#### Severe hypoglycaemia

Severe hypoglycaemia is a suspsected hypoglycaemic event requiring treatment assistance from another person. Carbohydrates, parenteral glucose or glucagon has to be actively administered to restore plasma glucose to normal. Plasma glucose measurements may or may not be available during such an event. The need of treatment assistance and adequate response to treatment is considered sufficient evidence that the event was induced by a low plasma glucose concentration. These episodes may be associated with sufficient neuroglycopenia to induce seizure or coma [15]. The patient must report all events of severe hypoglycaemia within 24 h by telephone to a nurse. Like in daily clinical practice investigators must encourage patients to report all episodes of severe hypoglycaemia at the quarterly visits at the outpatient clinics, hereby minimizing the risk of missing events.

A structured interview questionnaire will be applied to all possible severe hypoglycaemic episodes in order to validate episodes according to Whipple’s triad [26]. All episodes will be adjudicated by an independent endpoint committee consisting of diabetes specialists blinded to the individual patient insulin regimen.

### Additional hypoglycaemia assessment

#### In-hospital overnight glucose profiles

Patients are invited (optional) to stay overnight at Nordsjællands Hospital Hillerød four times during the study (after 6 and 12 months in each treatment arm). At the evening of the overnight stay the participants take part of a standard meal. Afterwards the participants are accommodated, and a venous line is inserted in an antecubital vein. During the night, blinded samples for subsequent plasma glucose measurements are drawn every hour from the catheter, while the patient is asleep [27].

#### Continuous glucose monitoring (CGM)

Optionally interstitial glucose concentrations are assessed twice for six days in each treatment arm using the CGM device iPro®2 digital recorder, MMT-7741 (iPro2) with the Enlite® sensor (MMT-7008 (Glucose sensor), Medtronic Minimed, Northridge, USA). The sensor is mounted by a trained study nurse and the patient is instructed how to calibrate the device, using capillary glucose measurements. The device is mounted in connection with visit 3, 5, 7 and 9 (after 6 and 12 months in each treatment arm).

After six days the glucose recorder is collected, and data are uploaded into CareLink iPro Therapy Management Software for Diabetes (CareLink iPro, MMT-7340) to generate reports and store data. These data remain blinded to the investigators until the end of the study and are not used to control glycaemic levels during the study period.

### HbA1c assessment

At every visit to the outpatient clinic (excluding V0) blood samples are drawn to measure HbA1c levels (analysed centrally at Nordsjællands Hospital).

## Statistics

### Power considerations

Rates and distribution of hypoglycaemic events are much skewed and unpredictable [6, 28]. The occurrence of hypoglycaemia is influenced by many factors, and by engaging in a study rates of hypoglycaemia usually are affected considerably.

Formal power calculations are therefore, not found feasible.

According to the power calculation and results from the HypoAna trial with a significant relative difference between treatment regimens of 30–40% concerning both primary and secondary nocturnal endpoints [5, 6, 8], we decided to include and randomise approximately 175 type 1 diabetes patients prone to severe hypoglycaemia (i.e. one or more episodes of nocturnal severe hypoglycaemia during the preceding two years).

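### The stated size of about 175 randomised patients cannot be reconciled with 154 screened and closed inclusion, and the article does not say the target was missed

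*Protocol article*

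**What the plan says.** Under Power considerations, the protocol article reports the design decision: "we decided to include and randomise approximately 175 type 1 diabetes patients prone to severe hypoglycaemia". Just before this it says of the present trial: "Formal power calculations are therefore, not found feasible". It then supports 175 by pointing to the power calculation and results of the HypoAna trial, with a 30–40% relative difference (references 5, 6 and 8).

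Under Screening, in- and exclusion criteria, it says that patients with the qualifying history "are screened (*n* = 154) according to in- and exclusion criteria". The same section adds: "Participants were included in the HypoDeg Trial from January 2015 to February 2017" and "Last patient, last visit expected in February 2019". It also says that patients who stop are not replaced, but that their data stay in the intention-to-treat analysis.

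Visit procedures give the order of steps. At visit 0 "patients are screened for in- and exclusion criteria and eligible patients are scheduled for enrolment in the treatment phase of the study", and randomisation follows at visit 1.

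The number actually randomised is not given anywhere, and neither a missed target nor a revised one is mentioned.

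**The concern.** Only screened patients can be randomised. A screened total of 154 with recruitment finished cannot lead to about 175 randomised, yet the article prints both figures without comment. A reader who takes the size from the statistics section will credit the trial with more precision than it can have. This matters most if the result is null or imprecise.

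A second, smaller matter is the basis for 175. The text does not spell out that the effect and the power calculation it cites were obtained in another trial, and apparently for another insulin comparison. A reader could take 30–40% as the difference this trial was sized to detect between degludec and glargine U100.

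**Working it through.** **Inputs from the article**
- Design target: about 175 randomised (Power considerations).
- Screened: 154 (Screening, in- and exclusion criteria).
- Inclusion: January 2015 to February 2017; last visit expected February 2019 (same section).
- Two treatment periods of 12 months each (Design).
- Screening at visit 0, randomisation at visit 1 (Visit procedures).
- Two-sided 5% significance level (Planned analyses).

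**Can 175 be reproduced?** No. The article gives no power, event rate, dispersion or dropout. As an illustration, take a paired normal approximation on the log-rate difference, n = ((1.96 + z_power) × SD / ln RR)². At 80% power, n = 175 needs an SD of 1.68 for a rate ratio of 0.70, or 2.41 for 0.60. Over an assumed SD of 0.8 to 2.4 and power of 80% or 90%, n runs from 40 to 476 (rate ratio 0.70) and from 20 to 232 (0.60). So 175 can be neither confirmed nor called numerically wrong. It is a target, and the check below is whether it could be reached.

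**Was recruitment finished?** Inclusion is reported in the past tense. February 2017 plus 2 × 12 months is February 2019, which matches the expected last visit. The dates leave no room for later enrolment.

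**Shortfall.** Randomised ≤ screened = 154.
- 175 − 154 = 21 patients.
- 154 / 175 = 0.88, so the shortfall is at least 12%.
- Allowing 3% for the word approximately (my assumption) covers 0.03 × 175 = 5.25 patients, not 21.

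**Precision.** Standard errors scale with 1/√n: √(175/154) = 1.066, so at least 6.6% larger. This bound supposes no screen failures. With an assumed 10% screen failure, 0.90 × 154 = 138.6 remain and the factor is √(175/138.6) = 1.124. With an assumed 20%, 123.2 remain and the factor is 1.192.

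**Power, illustrative only**, because the article states none: Φ((1.96 + z_power) × √(154/175) − 1.96).
- If 175 gave 80%: Φ(2.80 × 0.938 − 1.96) = 0.748.
- If 175 gave 90%: Φ(3.24 × 0.938 − 1.96) = 0.860.

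**Source of the 30–40%.** Power considerations cite references 5, 6 and 8 for it. The Design section identifies HypoAna as reference 5. The Background cites references 5–8 for this statement: "Insulin detemir reduces the risk of nocturnal (severe and non-severe) hypoglycaemia even in patients with type 1 diabetes". The link to detemir therefore runs through shared reference numbers. The Background itself prints no 30–40% figure; its only range for a reduction in nocturnal hypoglycaemia is 26–53%, for glargine and detemir against NPH (references 2–4).

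**The case against.** The strongest reply is that a target and an achieved count are different things. Power considerations record a past decision, and missing a target does not make that record false. This stands: 175 should not be deleted. It does not excuse an article that reports closed recruitment, gives a screened count below the target and leaves the two unreconciled.

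It can also be said that 154 may count something else. If it is the number enrolled, it is mislabelled and 175 was still missed. If it is a partial count, that sits badly with closed inclusion and needs a label. Each reading needs a correction. An article may leave sample-size detail to the full protocol, but that does not cover two printed figures that conflict.

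Three stronger readings are tempting and are not supported.

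- A reader might infer that the justification contradicts itself, since a power calculation is called infeasible and then relied on. The natural reading is that the second reference is to the earlier trial's own calculation. Borrowing a size in this way is weak, but it is not a contradiction.
- A reader might say that the Background attributes the 30–40% to detemir. It does not print that figure. The link is a plausible inference from reference numbers, and the cited sources are not at hand.
- A reader might add 10–25% attrition to 154 and arrive at 62–70% power. That compares 175 without losses with 154 after losses. With the same loss fraction d on both sides, 154(1 − d) / 175(1 − d) is still 0.88 and the power is still about 75%. It also discards patients whose data the intention-to-treat analysis keeps.

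**Conclusion.** The point holds as a failure to reconcile the stated size with the reported accrual. On the article's own figures, at most 154 patients were randomised. This is at least 21 (12%) below the stated size, with standard errors at least 6.6% larger, and the article does not say so. These bounds rest on one assumption: that 154 is the total entering formal screening, which is how the sentence reads. The 75% and 86% power figures rest in addition on a starting power of 80% or 90% that the article never states, and should not be quoted as this trial's power.

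On the basis for 175, the conclusion is limited to clarity. The article names the earlier trial but does not say that its effect and calculation were not derived for degludec versus glargine U100. The design and the analysis are unaffected. This is a reporting correction that should be made.

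**What to change.** 1. Keep 175 in Power considerations as the design target. Beside it, give the number actually randomised and say that the target was not reached. If 154 is not the total screened, say in the criteria section what it counts.
2. Reword the basis for 175: the 30–40% difference and the power calculation come from the earlier trial. State which insulins that trial compared, and that neither figure was calculated for degludec versus glargine U100.
3. Optionally, give the detectable rate ratio or expected confidence interval width at the achieved size, with its assumptions shown. It could use pooled event rates and dispersion without the randomisation code, since the article says the analysis plan is settled before that code is added to the cleaned data.

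Items 1 and 2 cost a few sentences and item 3 one calculation. No enrolment, analysis or clinical procedure changes. The price is that the size readers see becomes less favourable.
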